### Trial design and setting

Due to the logistical reasons discussed above, a non-randomised controlled clinical trial will be performed. The measurement points of both groups will be comparable, matching gender, age, geographical area of residence and diagnosis. Fig 1 shows the SPIRIT 2013 schedule of enrollment, interventions, and assessments. Fig 2 includes a flow chart of the main parts of the study methods.

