### Data collection

Outcome variables will be assessed in both study groups at the beginning of the COT-MHABI protocol, 6 months after the start of the protocol, and after the end of the protocol (12 months) using the scales detailed in Table 2. The collection will be carried out by different researchers. To minimise potential discrepancies, one researcher will allways evaluate the same participant.

**Table 2 pone.0274193.t002:** Tests and variables used in the data analysis.

Test	Outcome variable definition	Scores and Domains	Reliability
*Main outcomes*			
WHOQoL-BREF	Quality of life	**Quality of life (Total score: Min 26-Max 130)** (Domains: general QoL, health status satisfaction, physical health, psychological health, social relationship and environment)	ICC = 0.87
COPM	Self-perceived occupational performance	**Performance change**: difference between measures in self-perceived occupational performance **(Total score: Min 0-Max 50)** **Satisfaction change**: difference between measures in occupational performance satisfaction **(Total score: Min 0-Max 50)**	r = 0.87–0.88
*Secondary Outcomes*			
SOD-EO	Satisfaction with daily occupation, occupational balance and activity level	**Satisfaction (Score: Min 13-Max 91)** Activity level (Score: Min 0-Max 13) Occupational Balance (Score: profile, no min or max) (Domains: productivity, leisure, home tasks and selfcare).	r = 0.84–0.92
RCv3	Satisfaction with performed roles	**Satisfaction (Score: Min 0.00-Max 1.00)** Number of performed roles (Score: Min 0-Max 10) Participation (Score: Min 0.00-Max 1.00) Desired Performance (Score: Min 0.00-Max 1.00)	r = 0.74–1.00
ACS	Perceived activity participation level	**Percentage of maintained activities after ABI (Total score: Min 0%-Max 100%)** (Domains: instrumental activities, low physical demand leisure activities, high physical demand leisure activities, social and educational activities)	r = 0.88–0.95
CIQ	Community integration and participation	**Community integration and participation (Total score: Min 0-Max 29)** (Domains: home integration, social integration and productivity)	r = 0.83–0.93
FIM	Functional Independence	**Functional Independence (Total score: Min 18-Max 126)** (Domains: motor and cognitive)	ICC = 0.85

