### Statistical analysis

Data will be analysed on an intention-to-treat basis [61] i.e. results will be analysed using the basis of all participants. For missing data, the multiple imputation method will be used.

All variables will first be checked for normality. To test the effectiveness of the intervention, continuous variables having normal distribution will be analysed by repeated measures analysis of variance, ANOVA (within-subject factors: baseline, intermediate evaluation, final evaluation), comparing the two groups (between-group factors).

Due to the proposed design and the technical feasibility of the experimental group provider site, non-simultaneous recruitment makes the potential exposure to certain external factors unequal for some subjects. These factors may include the season of the year or the phase corresponding to the COVID-19 pandemic situation. To control them, we will explore the differences in the proportion of participants for these variables between the two groups using chi-square tests. If there are differences between groups an ANCOVA will be carry out with these external factors as covariates.

Non-normally distributed variables will be analysed using the Mann-Whitney test for group comparison. Friedman analyses and the Wilcoxon signed-rank test will be used for intrasubject factors. A p value < .05 will be defined as statistically significant. Bonferroni correction will be carried out for planned comparisons.

To determine the contribution of satisfaction with activities on quality of life in people with brain injury and a diagnosis of mental illness, beyond the intervention performed, a hierarchical regression analysis will be performed with the entire sample, including the following variables in model 1: belonging to the intervention group, age and level of functionality. In model 2, in addition to the variables in model 1, the variable satisfaction with the occupation (collected by SDO-OB) will be added.

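### The COVID-19 phase check names no visit and reads as one value per participant, so a month-12 difference in phase between arms can pass unseen and unadjusted

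*Protocol article*

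**What the plan says.** The protocol article, Statistical analysis, recognises the problem itself: "non-simultaneous recruitment makes the potential exposure to certain external factors unequal for some subjects". It gives examples: "These factors may include the season of the year or the phase corresponding to the COVID-19 pandemic situation". The control has two steps. First, "we will explore the differences in the proportion of participants for these variables between the two groups using chi-square tests". Second, "If there are differences between groups an ANCOVA will be carry out with these external factors as covariates". Neither step says at which visit a participant's season or phase is taken.

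The Data collection section sets the visits: "Outcome variables will be assessed in both study groups at the beginning of the COT-MHABI protocol, 6 months after the start of the protocol", with a last assessment at 12 months. The main analysis for normally distributed outcomes is a repeated-measures ANOVA over these three occasions with group as the between-subject factor.

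Under Trial design and setting the trial is non-randomised, and "The measurement points of both groups will be comparable, matching gender, age, geographical area of residence and diagnosis". Calendar time is not in that list. Controls come from the waiting list (Recruitment methods).

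**The concern.** A chi-square test on proportions of participants needs one category per participant, and a conventional ANCOVA covariate in a repeated-measures ANOVA is also one value per subject. Pandemic phase is a property of a date. A participant followed for a year may be scored in one phase at entry and in another at month 12. If the category is taken at entry, the check says nothing about conditions at the visit where the effect is read.

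The trial is not randomised and calendar time is not matched, so this step is the plan's only stated protection against a bias that it names. Community integration, activity participation and role outcomes could plausibly move with restrictions. If conditions change between baseline and month 12 differently in the two arms, that difference would be read as an effect of the intervention.

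**Working it through.** **Plan's own figure.** A two-sided two-sample t-test with d = 0.49, alpha 0.05 and power 0.80 gives 67 per arm, 134 in total (power 0.804). The stated sample size reproduces and is not in question; 67 per arm is used below.

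**Season.** For each of the 12 possible start months, the season at month 12 equals the season at baseline, and the season at month 6 is the opposite one. Arms balanced on season at entry are therefore balanced at all three nominal visits. Only visit slippage breaks this. With an assumed uniform window of ±1 month, the mean shift is 0.5 month against a 3-month season, so 0.5/3, or about 17%, of participants change category. That biases the comparison only if slippage differs by arm.

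**COVID-19 phase: formula.** Let a phase shift the score by g (in SD), and let E0, E12, C0 and C12 be the proportions of the experimental and control arms in that phase at baseline and month 12. With no treatment effect:

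bias in the difference of change = g × [(E12 − E0) − (C12 − C0)].

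If the entry check finds the arms equal (E0 = C0), this becomes g × (E12 − C12). An ANCOVA on entry phase estimates the raw arm difference minus a slope times the arm difference in mean entry phase. That second term is zero when entry is balanced, so the adjustment leaves the bias in place whatever the slope.

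**Assumed example.** The article gives no dates, so phases are assumed to change at calendar months 12 and 18, with the middle phase shifting the score by g. Everyone enters before month 12, so all are in the first phase at entry: the chi-square cannot trigger, and entry phase is constant as a covariate. This is so by construction.

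- Recruitment in months 0–6 vs 6–12: E12 = 1, C12 = 0, difference 1.00, bias = g.
- Recruitment in months 0–8 vs 4–12: the month-12 visit falls in the middle phase if entry is before month 6. E12 = 6/8 = 0.75, C12 = 2/8 = 0.25, difference 0.50, bias = 0.5g.
- Same window in both arms: difference 0, bias 0.

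With within-person correlation 0.5, the SD of change is √(2 × 0.5) = 1 and the standard error of the difference is √(2/67) = 0.173. For g = 0.5 with windows 0–8 vs 4–12, 0.25/0.173 = 1.45, which gives a false-positive rate of about 0.30.

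Simulation (2,000 runs per setting, no treatment effect, change from baseline to month 12) gave:

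| Windows | g (SD) | Bias, unadjusted or entry-phase ANCOVA | False-positive rate | Bias with month-12 phase added | False-positive rate |
|---|---|---|---|---|---|
| 0–6 vs 6–12 | 0.1 | 0.097 | 0.096 | not estimable | – |
| | 0.2 | 0.204 | 0.214 | not estimable | – |
| | 0.3 | 0.299 | 0.414 | not estimable | – |
| | 0.5 | 0.503 | 0.831 | not estimable | – |
| 0–8 vs 4–12 | 0.1 | 0.045 | 0.057 | −0.005 | 0.054 |
| | 0.2 | 0.097 | 0.091 | −0.002 | 0.049 |
| | 0.3 | 0.142 | 0.126 | −0.006 | 0.056 |
| | 0.5 | 0.250 | 0.298 | 0.001 | 0.056 |
| 0–12 in both | 0.1–0.5 | about 0 | 0.047–0.055 | about 0 | 0.049–0.055 |

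**A case where entry phase varies.** Assume both arms are 50% in a restriction phase at entry but 37% vs 63% at month 12, with within-person correlation 0.6. The bias is 0.3 × 0.26 = 0.08 SD to 0.5 × 0.26 = 0.13 SD, that is 0.078/0.49 = 16% to 0.13/0.49 = 27% of the planned effect. The standard error is √(0.8 × 2/67) = 0.155, so false-positive rates are about 8% to 13%. A simulation at 0.5 SD gave a bias of 0.133 unadjusted, 0.133 with entry phase and 0.005 with phase coded at each visit, with rejection rates of 0.132, 0.133 and 0.045.

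**The case against.** The strongest reply is that the article never says the category is taken at entry. A chi-square can be run at each visit, and the ANCOVA sentence does not limit the covariates to entry values. Where the recruitment windows overlap, month-12 phase as a covariate brought the bias to about zero, so an ANCOVA within the current wording can work. The date on which a covariate is coded might also be left to a fuller document. And the examples were chosen so that entry is balanced while month 12 is not; with a common window there is no bias.

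Much of this stands. One value per participant is an inference from how the check is described, not a statement in the text, and the sizes show what is possible rather than what to expect. What does not fall away is that the article fixes a method for a bias it has named. On its natural reading, that method looks at one time point although the outcome is scored at three. The statement that the groups' measurement points will be comparable does not close the gap, since the listed matching variables exclude calendar time and the article itself says recruitment is not simultaneous.

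A reader might go further and infer that season suffers in the same way, or that no ANCOVA could remove the bias. The documents support neither. Baseline season fixes the season at the later nominal visits, and the failure belongs to an entry-phase covariate, not to ANCOVA as such.

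**Conclusion.** The point holds for COVID-19 phase, on the natural reading that each participant is classified once, at entry. Balance at entry does not imply balance at month 12; the check would then not lead to adjustment, and adjusting for entry phase would leave the bias where it is. This part follows from the formula and needs no simulation.

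The size cannot be estimated from the article. It depends on recruitment windows, phase boundaries, phase effects and within-person correlation, none of which is given. Across the assumed settings the false-positive rate ran from the nominal 5% (common window) to 83% (no overlap, 0.5 SD effect). The calculations use the change from baseline to month 12, a simplification of the planned three-occasion ANOVA.

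This is a cheap improvement to a stated method, not proof that the trial's result will be biased.

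**What to change.** Derive COVID-19 phase from the date of every visit, using phase boundaries set without sight of the outcomes. Tabulate it by arm at baseline, 6 and 12 months. Enter it as a visit-level covariate, either in a linear mixed model with arm, visit and arm-by-visit, or as visit-specific phase in an ANCOVA of the month-12 outcome. Season needs no such change at nominal visits.

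Report the calendar overlap between the arms, and state that without overlap phase and arm are confounded and no model can separate them.

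The cost is a few sentences in the plan, some coding from visit dates and a small loss of degrees of freedom.

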### Recruitment methods

For both the experimental and control groups, the referral of patients to the study will take place through the neuropsychiatry department of the Institut Guttmann Neurorehabilitation Hospital in Badalona (Spain), which does not participate in the al-location of subjects, protocol intervention, data collection, or statistical analysis of the results. This department will assess mental health baseline status using the Neuropsychiatric Inventory Questionnaire (NPI-Q)) [43], evaluating possible interference with the results of concomitant pharmacological treatment.

Regarding the allocation, the experimental group will be composed of patients that will receive the COT-MHABI intervention protocol, framed within a community intervention programme at the hospital, after discharge. As it is a very specific and novel intervention, the resources for its implementation are limited, generating a waiting list (over 12 months). Given that this standby period is longer than the duration of the intervention in the experimental group, patients on the waiting list will be invited to participate in the control group with the consideration of receiving the intervention at a later stage.

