#### Power analysis and sample size calculations

Theoretically, with a two-tailed test, a sample of 134 participants will be needed in order to detect a significant difference in WHOQoL-BREF showing an effect size d = 0.49 (alpha = 0.05, beta = 0.20, power = 0.80), according to data collected in Chiu et al. (2016) [47]. The sample was calculated using the GPower 3.1 program.

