### Limitations

Due to the technical feasibility of the programme, where the intervention is carried out, the clinical and social complexity of this patient profile, the lack of evidence on similar programmes and interventions, and the difficulties in finding a population in the setting that falls within the range of the inclusion and exclusion criteria, the presence of these issues that may interfere with the results and lead to bias should be highlighted.

The following have been identified as the main ones: (i) the inclusion of various aetiologies of ABI as a generalised concept, when the clinics presented by the patients may differ considerably [62]; (ii) the difficulty of knowing the influence of the different treatments that the patients in the control group may receive; (iii) the variability in the different conceptions of the construct "mental health" and its implications in the design of the protocol itself as well as in the practice on the quality of professional support that this population profile receives; (iv) due to the technical particularities of the research proposal, the therapist delivering the intervention and subsequently analysing a large part of the data is the same person, which may lead to biases in the results; (v) the heterogeneity in terms of the range of time after ABI in which the intervention takes place, as both groups have a wide range. This is because, at present, this is the first time that this type of support initiative is being provided in this region; so, patients are not screened according to the time of acquisition of the brain injury but by the importance of the current condition and their personal, occupational, social, and family issues.

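### In a non-randomised comparison, effectiveness is tested without clinical covariates, and adjustment is foreseen only for external recruitment factors that fail a chi-square test; time since ABI is neither matched nor adjusted for

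*Protocol article*

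**What the plan says.** - **Design.** Under Trial design and setting, "a non-randomised controlled clinical trial will be performed". Under Recruitment methods, limited programme capacity creates a waiting list of more than 12 months, and "patients on the waiting list will be invited to participate in the control group".
- **Control at the design stage.** The two groups are made comparable by "matching gender, age, geographical area of residence and diagnosis". Time since injury is not on that list. Injury severity is not named, although both medium and severe ABI are eligible.
- **Effectiveness analysis.** Normally distributed outcomes go to a repeated measures ANOVA with three visits and group as factors. Other outcomes go to the Mann-Whitney test. Neither is given covariates.
- **Adjustment rule.** External factors arising from non-simultaneous recruitment are compared between groups by chi-square tests. Season and pandemic phase are given as examples. Then: "If there are differences between groups an ANCOVA will be carry out with these external factors as covariates".
- **Baseline data.** Of the referring neuropsychiatry department, the article says: "This department will assess mental health baseline status using the Neuropsychiatric Inventory Questionnaire (NPI-Q"). FIM is measured at baseline as one of the secondary outcomes. Neither is in the effectiveness model.
- **Limitations.** Among the issues that may bias the results, the article names "the heterogeneity in terms of the range of time after ABI in which the intervention takes place, as both groups have a wide range".
- **Elsewhere.** Age and level of functionality stand beside group in the first step of the hierarchical regression on quality of life. That regression serves a different objective.

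**The concern.** Without randomisation, the group comparison is only as good as the control of factors that differ between arms and affect outcome. The plan has two tools: matching on four factors, and a conditional ANCOVA for external factors.

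The conditional ANCOVA lets a significance test decide which model is used. That test answers the wrong question: what matters is how large the imbalance is and how strongly the factor predicts outcome, not whether the imbalance reaches p < .05.

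The rule also leaves out the factors most likely to matter clinically. The plan names time since ABI as a threat and then gives it no place in either tool. It treats age and functionality as relevant to quality of life in one regression but omits them from the effectiveness test on that same main outcome. What is at stake is whether a group difference on WHOQoL-BREF or COPM can be attributed to the intervention.

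**Working it through.** **1. Inputs.** From the article: "Theoretically, with a two-tailed test, a sample of 134 participants will be needed", "showing an effect size d = 0.49", alpha 0.05, power 0.80, and 67 per arm (Fig 2 legend). The level of the chi-square test is not stated separately; 0.05 is taken from the general significance rule. All imbalance and confounder sizes below are assumptions, because the documents give none.

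**2. The plan's own figure.** The normal approximation is n per arm = 2(1.960 + 0.842)² / 0.49² = 65.4, so 66. The exact two-sample t test gives 67 per arm, 134 in total, with power 0.804. The stated sample size reproduces.

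**3. Power of the chi-square rule.** For proportions p1 and p2 with mean p̄ and n = 67:

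power = Φ{ [|p1 − p2| − 1.96·√(2p̄(1 − p̄)/n)] / √([p1(1 − p1) + p2(1 − p2)]/n) }

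For 50% versus 65%: (0.15 − 1.96 × 0.0854) / 0.0844 = −0.206, and Φ = 0.42.

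| Imbalance | Power | Left unadjusted |
|---|---|---|
| 50% v 60% | 0.21 | 79% |
| 50% v 65% | 0.42 | 58% |
| 50% v 70% | 0.66 | 34% |

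A 15-point gap centred on one half (42.5% v 57.5%) gives 0.40.

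**4. Bias from an unadjusted binary confounder, simple two-group comparison.** Bias in SD = confounder effect × difference in prevalence. The rejection rate under no treatment effect comes from the noncentral t distribution with noncentrality bias × √(67/2).

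| Confounder effect | Imbalance | Bias (SD) | Share of 0.49 | False positives |
|---|---|---|---|---|
| 0.5 SD | 10 points | 0.05 | 10% | 6.0% |
| 0.5 SD | 15 points | 0.075 | 15% | 7.2% |
| 0.5 SD | 20 points | 0.10 | 20% | 8.9% |
| 0.8 SD | 10 points | 0.08 | 16% | 7.5% |
| 0.8 SD | 15 points | 0.12 | 24% | 10.6% |
| 0.8 SD | 20 points | 0.16 | 33% | 15.1% |

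**5. Check against the planned three-visit ANOVA.** Simulation with no treatment effect: 4,000 runs, assumed correlation 0.5 between visits, imbalance 50% v 65% or 50% v 70%. The Monte Carlo standard error near 5% is √(0.05 × 0.95/4000) = 0.34 points.

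| Confounder acts on | Group-by-time test | Between-group test |
|---|---|---|
| Level only, 0.5 SD | 0.059, 0.048 | 0.072, 0.094 |
| 12-month change, 0.5 SD | 0.066, 0.077 | 0.064, 0.063 |
| 12-month change, 0.8 SD | 0.091, 0.102 | 0.071, 0.075 |

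A pure level shift cancels algebraically in the group-by-time test, so the first entry of 0.059 is simulation noise. Always adjusting the 12-month change for the confounder gave 0.049 to 0.055. That is a different statistic from the group-by-time F test, but it shows that the nominal level is recovered.

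**6. The chi-square rule on its own.** For one binary factor that is subject to the rule, the false-positive rate of the tested-then-adjusted analysis of change was 0.050 to 0.057. The rule therefore does little damage to the factors it covers. The exposure lies in the factors it never reaches.

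**The case against.** The strongest reply has several parts.

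- **The article is condensed.** It sets a rule for one problem, non-simultaneous recruitment, and is merely silent on clinical covariates, which a fuller plan may list. This stands as a caution. But the article does state how effectiveness will be tested and when adjustment will happen, and that rule is badly fixed as written.
- **Season and COVID-19 phase are examples.** A reader might infer that they are the only covariates possible. The text leaves the list open. The class is still external factors, and time since ABI, NPI-Q and FIM are outside it.
- **Four factors are matched.** A reader might infer a wholly uncontrolled comparison of self-formed groups. That is not supported: the arms follow from programme capacity, both share one referral route, and only residual imbalance in the matched factors matters. The matching factor diagnosis is undefined and might even cover severity. Time since ABI is plainly not covered.
- **Baseline is one of the repeated measures.** A stable difference cancels in a group-by-time test, so not every imbalance becomes treatment effect. This is correct. But the article does not say whether the interaction or the between-group term is the test, and under the latter a stable difference does count.
- **The preliminary test barely changes type I error.** Also correct, as step 6 shows.
- **Severity imbalance is not shown.** It is tempting to read the Limitations remark that patients are screened by the importance of their current condition as evidence of unequal severity. It describes who enters the study, not who goes to which arm. Likewise, a wide range of time since ABI in both groups is heterogeneity, not demonstrated imbalance.
- **NPI-Q has a stated use**, namely to evaluate interference from concomitant drug treatment. The analysis section does not carry that into the effectiveness model.

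**Conclusion.** The concern holds in limited form. The effectiveness analysis of this non-randomised trial has no clinical covariates. Its one adjustment rule depends on a test that would miss a 15-point imbalance in about 58% to 60% of trials of this size. A factor that the article itself flags as a possible source of bias is neither matched nor modelled. Confounders that affect change can therefore be read as treatment effect, and so can stable differences if the between-group term is the test.

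The size cannot be derived from the documents. Under assumed biases of 0.08 to 0.16 SD, the distortion is 16% to 33% of d = 0.49, with about 7.5% to 15% false positives. A reader might take these as error rates of the planned ANOVA. They are not: they belong to a two-group comparison without baseline. In the three-visit simulation the group-by-time test reached 6.6% to 10.2%, and only when the confounder acted on change.

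**What to change.** - Delete the chi-square decision rule.
- Fix, before outcomes are seen, an effectiveness model that always includes a short set of baseline covariates: the four matching factors, time since ABI, baseline NPI-Q, baseline FIM, and season and COVID-19 phase coded coarsely. Timing matters because the Limitations section says the treating therapist also analyses much of the data. When FIM is itself the outcome, its baseline is already in the model.
- Enter each covariate with a covariate-by-visit term. A covariate that only shifts the level does nothing for a group-by-time test.
- State which term is the test of effectiveness.
- Say how the same covariates enter for outcomes that would go to the Mann-Whitney test, which takes none.
- Report standardised differences in place of balance tests, and keep the unadjusted analysis as a sensitivity analysis.

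**Cost.** The sample size does not change. With one degree of freedom for each of the nine covariates, error degrees of freedom for a 12-month change analysis fall from 132 to 123. If diagnosis had five categories (an assumption), it would take 4 instead of 1, and 120 would remain. Covariate-by-visit terms in the full three-visit model use more, hence the coarse coding. COVID-19 phase may be nearly collinear with group if the arms are recruited at different times, which would widen the interval for the treatment effect; that should be examined and reported. Time since ABI must be recorded at entry. The article does not say that it is, so its availability is an assumption. Changing the matching list is not advised, because that would alter recruitment in a population the article describes as hard to find.

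### Except for COPM, outcomes that fail the normality check are compared between non-randomised arms by a Mann-Whitney test with no baseline term

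*Protocol article*

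**What the plan says.** The Statistical analysis section sends every variable through a normality check. Normally distributed outcomes go to a repeated-measures "ANOVA (within-subject factors: baseline, intermediate evaluation, final evaluation), comparing the two groups (between-group factors"), so baseline is one of the time levels and a group-by-time contrast exists.

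For the rest, "Non-normally distributed variables will be analysed using the Mann-Whitney test for group comparison", and "Friedman analyses and the Wilcoxon signed-rank test will be used for intrasubject factors". The time point and the quantity entering the Mann-Whitney test (final score, score at each visit, or change) are not stated.

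The only covariate adjustment of an arm comparison concerns season and pandemic phase, and it is conditional: "If there are differences between groups an ANCOVA will be carry out with these external factors as covariates". The baseline score is not among these factors.

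Under Trial design and setting, "a non-randomised controlled clinical trial will be performed", with "matching gender, age, geographical area of residence and diagnosis". Recruitment methods adds that controls come from the waiting list. Data collection has the outcomes measured in both arms at baseline, 6 and 12 months. Table 2 defines the two COPM outcomes as differences between measures and gives the other outcomes as scores.

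**The concern.** Baseline scores are collected in both arms, yet in the non-normal branch nothing brings them into the comparison of the arms. Mann-Whitney has no place for a covariate. Friedman and Wilcoxon signed-rank tests describe movement within subjects and give no contrast of one arm's change with the other's.

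In a randomised trial this would mainly cost precision. Here nothing in the design makes baseline scores equal: allocation is not random, and matching covers no outcome score. A difference present before treatment would carry into the 12-month comparison, where it could mimic an effect or hide one.

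WHOQoL-BREF is a main outcome and the basis of the sample size, and it takes this route if it fails the check. So would SDO-OB satisfaction (13 to 91), RCv3 satisfaction (0 to 1), ACS (0 to 100%), CIQ (0 to 29) or FIM (18 to 126). Whether baseline is used at all then turns on a normality check made on the data.

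**Working it through.** **The plan's own figure.** A two-sample t test with d = 0.49, two-sided alpha 0.05 and power 0.80 needs 66.35 per arm, so 67 per arm and 134 in total. This is the stated number, and power at 67 per arm is 0.804. The sample size is not in dispute.

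**Inputs.** From the article: 67 per arm, two-sided 0.05, d = 0.49. Assumed, because the documents do not give them: a baseline to 12-month correlation ρ = 0.6, a baseline gap of 0.3 SD (0.2 SD as a variant), equal unit SDs and normal scores. Two mechanisms are considered:
- *Persistent gap*: the whole gap is still present at 12 months, so the final difference is 0.3 with no treatment effect.
- *Selection on the observed score*: the gap regresses, so the final difference is ρ × gap = 0.6 × 0.3 = 0.18.

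**Formula.** z = (expected difference / SD) × √(67/2) × √(3/π), where 3/π is the relative efficiency of the rank test under normality. The multiplier is 5.788 × 0.977 = 5.656. Rejection rate ≈ Φ(z − 1.96) + Φ(−z − 1.96). Using the same multiplier for rank ANCOVA is an approximation.

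- Mann-Whitney on final score, SD 1: z = 0.3 × 5.656 = 1.697 (persistent) and 0.18 × 5.656 = 1.018 (selection).
- Rank ANCOVA, residual SD √(1 − 0.36) = 0.8: the remaining difference is 0.3 − 0.18 = 0.12 (persistent), so z = 0.15 × 5.656 = 0.848. Under selection it is 0.18 − 0.18 = 0.
- Mann-Whitney on change, SD √(2 × 0.4) = 0.894: the difference is 0 (persistent). Under selection it is 0.18 − 0.30 = −0.12, so |z| = 0.134 × 5.656 = 0.759, in the direction opposite to the gap.

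| False-positive rate, 0.3 SD gap | Persistent: formula / simulation | Selection: formula / simulation |
|---|---|---|
| Mann-Whitney, final score | 40% / 39% | 17% / 18% |
| Rank ANCOVA | 14% / 14% | 5% / 5% |
| Mann-Whitney, change | 5% / 5% | 12% / 12% |

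**Smaller gap.** At 0.2 SD, Mann-Whitney on final scores gives z = 1.131 and 0.679, about 20% and 10%. Simulation gives about 18 to 21% for the persistent gap and 10% for selection.

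**Other correlations and skewed scores.** A separate simulation used correlations of 0.5 and 0.7 and both normal and gamma-skewed scores. At a 0.3 SD gap, Mann-Whitney on final scores rejected in 38 to 49% of trials when the gap persisted and 14 to 28% when it regressed. The upper ends came from the skewed scores, which are the kind this branch is meant for.

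**No gap.** All tests reject at about 5%. At d = 0.49, simulated power is 0.78 for Mann-Whitney on final scores and 0.92 for rank ANCOVA. The formula gives z = 0.49 × 5.656 = 2.771, power 0.79, and z = (0.49/0.8) × 5.656 = 3.464, power 0.93.

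**The case against.** The best defence is that a journal article condenses. It names a test and leaves the analysed quantity to a fuller plan. If change from baseline is what the sponsor means to compare, baseline is already used. This stands in part: the text does not tie the Mann-Whitney test to final scores. But Table 2 labels only COPM as change, so comparing scores is the plain reading for everything else, and if change is meant the article should say so. The point also does not rest on an omission, since the article names the test and that test cannot take a baseline term.

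Three stronger readings are tempting and are not supported:

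- *Every non-normal outcome is tested without regard to baseline.* This is not so for COPM. A Mann-Whitney test on its Table 2 outcomes is a between-arm test of change.
- *A baseline gap is likely.* A reader might infer this from Limitations, where patients are said to be screened "by the importance of the current condition and their personal, occupational, social, and family issues". That sentence explains the wide range of time since injury in both groups and does not contrast the arms. Both arms share the same eligibility criteria and the same referring department, which takes no part in allocation. Non-random allocation makes a gap possible; no passage shows one or gives its size.
- *Baseline adjustment is the best choice however a gap arose.* It is not. Under a persistent gap rank ANCOVA keeps 14% false positives where change has 5%; under selection the figures are 5% and 12%. The trade-off between adjustment and change applies in this branch too. What the figures show is that both do better than an unadjusted final score when there is a gap.

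It is also fair to say that the inflation requires an outcome to fail the normality check, which the documents cannot settle.

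**Conclusion.** The point holds in a limited form. Except for the COPM outcomes, the non-normal branch compares the arms with a test that has no baseline term, names no change score, and tests change only within subjects. In a non-randomised trial whose matching leaves out outcome scores, this lets any baseline gap in WHOQoL-BREF or a secondary scale pass into the estimated effect, on the reading that scores are compared.

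The rates of about 39% and 18% describe what an assumed 0.3 SD gap at an assumed correlation of 0.6 would do; they do not predict this trial. Without a gap, error is held at 5% and the cost is precision alone. Because the alternative helps in either case, this is more than a request for detail.

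**What to change.** For non-normal outcomes not already defined as change, replace the unadjusted Mann-Whitney comparison with a baseline-adjusted comparison of the 12-month score, named in advance as primary. Rank ANCOVA would serve, or an ordinal model with the baseline score as covariate. In the same branch, report a between-arm Mann-Whitney test of change from baseline as a sensitivity analysis. State that the within-arm Friedman and Wilcoxon tests are descriptive and are not evidence of effectiveness.

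The cost is analysis wording only: no new data, visits or patients. It should be settled before outcomes are analysed. The downside is that baseline adjustment leaves part of a fully persistent gap in the estimate. The change analysis is there to show this, and if the two disagree the report should say so.
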